#### Mediators

Health status will be assessed by the Chinese (Hong Kong) Short-Form-12 [23], which is a 12-item scale that can yield both physical health and mental health components. A higher respective summary score indicates better levels of health.

Rumination will be assessed by the rumination subscale from the Rumination-Reflection Questionnaire [24]. The subscale consists of 12 items that can assess recurrent thinking or rumination about the self, prompted by threats, losses, or injustices to the self. A higher score suggests greater ruminative tendencies.

Hyperarousal will be assessed by the hyperarousal scale [25]. It is a 26-item scale that can measure tendencies toward introspection, thinking about feelings, responding intensely to unexpected stimuli, and other behaviours that putatively involve cortical arousal. A higher score suggests a higher arousal level.

### Qualitative focus group interviews

One-fourth of the participants will be selected and invited from each intervention group for focus group interviews at T4. The format of the group interviews will be semi-structured, with a collaborative enquiry of the experiences gained from the respective interventions. The practicability of the programme, perceived therapeutic ingredients, and perceptions of the benefits regarding improvements in sleep disturbances from the participants’ perspectives will be explored and identified through the focus group interviews.

### Ethical considerations

This proposal has been approved by Human Subjects Ethics Sub-committee from the Hong Kong Polytechnic University (Reference number: HSEARS20210331002-01). An information sheet and a written consent form which has been formally approved by the ethics committee will be distributed to participants when they are invited to take part in the research project. Participation in this study will not make excessive discomfort or other injuries. Observation of mental state and any potential of self-harm behaviours will be closely taken throughout the processes of respective interventions or assessments. When necessary, participants would be advised to consult a professional. Individuals may experience some mild discomforts or tiredness during the MBTCC, MBI, or TCC programme. Such discomforts or fatigue, however, should be no greater than what they experience in everyday life. On the other hand, the participants may get direct therapeutic benefits of improving their sleep problems by taking part in respective interventions. Participants are free to decide whether to participate in this study, and they can revoke their consent and withdraw from the study at any time during the study, without any reason. This decision will not affect their medical care, nor will it cause any unpleasant results.

Informed consent will be obtained in accordance with the Declaration of Helsinki. The investigator will prepare the informed consent form which has been approved by the ethical committee. A properly executed, written, informed consent will be obtained from each participant prior to entering the participant into the trial. Information will be given in both oral and written form and participants will be given ample opportunity to inquire about details of the study. A copy of the signed consent form will be given to the participant, and the original will be maintained with the participant’s records. Any information obtained in this study will remain very strictly confidential, will be known to no one, and will be used for research purposes only. Codes, not names, are used on all test instruments to protect confidentiality. Data will be stored in encrypted files on the computer.

A participant may be discontinued from study treatment at any time if the participant or the investigator feels that it is not in the participant’s best interest to continue. There is a list of possible reasons for study treatment discontinuation: (1) the participant’s withdrawal of consent, (2) the participant is not compliant with study procedures, (3) the occurrence of adverse events so that the investigator would be in the best interest of the participant to discontinue his/her study treatment, (4) protocol violation requiring discontinuation of study treatment, and (5) lost to follow-up. All participants are free to withdraw from participation at any time, for any reasons, specified or unspecified, and without prejudice.

A trial steering committee which is composed of the first author, the corresponding author, and two invited independent expert members will be formed. The major goal of this committee is to monitor and supervise the progress of the study towards its overall objectives and ensure adherence to the protocol, patient safety, and consideration of new information relevant to the research question. In addition, the corresponding author will be responsible for all aspects of coordinating all local organizations including identifying potential recruits and taking consent. The committee will meet once every 3 months over the course of the trial to oversee conduct and progress.

### Data management

The investigator will prepare and maintain adequate and accurate source documents designed to record all observations and other pertinent data for each participant treated with different interventions. Participants will not be identified by name in the study database but will be identified by a participant code. The investigator is responsible for all information collected on participants enrolled in this study. All data collected during the course of this study must be reviewed and verified for completeness and accuracy by the investigator.

The data will be entered into a validated database. Database lock will occur once quality assurance procedures have been completed. All procedures for the handling and analysis of data will be conducted using good computing practices for the handling and analysis of data for clinical trials. After data have been entered into the study database, a system of computerized data validation checks will be implemented and applied to the database on a regular basis. The study database will be updated in accordance with the resolved queries. All changes to the study database will be documented.

The database is safeguarded against unauthorized access by established security procedures; appropriate backup copies of the database and related software files will be maintained. Databases are backed up by the database administrator in conjunction with any updates or changes to the database. At critical junctures of the protocol (e.g. production of interim reports and final reports), data for analysis is locked and cleaned per established procedures.

A data monitoring committee which is composed of the corresponding author, an independent biostatistician, and two invited independent expert members experienced in clinical trials will be formed. The major goal of this committee is to regularly review and maintain the confidentiality of the accumulating data in this trial. The independence of this committee is also to safeguard the interests of the participants and enhance the integrity of this trial. The committee will meet once every 3 months over the course of the trial to oversee conduct and progress.

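### The data monitoring committee is described as independent, but one of its four members is the corresponding author, who helps steer the trial and is responsible for coordinating recruitment and consent

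*Protocol article*

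**What the plan says.** Two sections of the protocol article bear on this.

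**Data management.** The membership is given as "A data monitoring committee which is composed of the corresponding author, an independent biostatistician, and two invited independent expert members". The task is stated as follows: "The major goal of this committee is to regularly review and maintain the confidentiality of the accumulating data in this trial". The claimed safeguard comes next: "The independence of this committee is also to safeguard the interests of the participants and enhance the integrity of this trial". On frequency: "The committee will meet once every 3 months over the course of the trial to oversee conduct and progress".

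**Ethical considerations.** The steering committee is described in similar terms: "A trial steering committee which is composed of the first author, the corresponding author, and two invited independent expert members will be formed". It also meets every 3 months, and its remit includes weighing new information that bears on the research question. The article adds that "the corresponding author will be responsible for all aspects of coordinating all local organizations including identifying potential recruits and taking consent".

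Neither section mentions a closed session, a non-voting seat or a recusal for the corresponding author.

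**The concern.** A data monitoring committee keeps emerging results confidential chiefly from the people who run the trial, because knowledge of a trend can influence how they run it. Here one of those people is a member. The article itself applies the word independent to the other three members and not to this one, yet claims independence for the committee as a whole.

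This matters more in this trial than in some others. The primary outcome, the Insomnia Severity Index, is self-reported. Participants attend visibly different programmes. Enrolment is planned over more than two and a half years, so early participants will be supplying outcome data while later ones are still being approached. The trial team keeps discretion over how the study is explained, over the monthly calls about home practice, and over discontinuation from study treatment when the investigator judges it to be in the participant's interest. The corresponding author's seat on the steering committee gives a direct route from what the monitoring committee sees to decisions on conduct.

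**Working it through.** No formula in the plan is at issue, and there is no stated figure to reproduce. The check sets the sections side by side and counts the scheduled meetings.

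**1. Membership against the claim**

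| Data monitoring committee member | Called independent in the article? | Other stated role |
|---|---|---|
| Corresponding author | No | Steering committee member; responsible for coordinating centres, including recruitment and consent |
| Biostatistician | Yes | None stated |
| Invited expert 1 | Yes | None stated |
| Invited expert 2 | Yes | None stated |

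Members with a role in trial conduct: 1 of 4, or 25%. The claim of independence is made for the whole committee, so one such member is enough to contradict it.

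**2. Is this only missing detail?** No. Membership, purpose, claimed independence and meeting frequency are all stated. A charter or the full protocol could add a closed session, but the published membership would still conflict with the published claim.

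**3. How often could accumulating data reach this member during enrolment?**

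- Expected recruitment (Trial status): 1 September 2022 to 18 April 2025, about 31.5 months.
- Meeting interval (Data management): 3 months.
- Meetings: 31.5 / 3 = 10.5, so about 10 during recruitment. This assumes that the committee starts when recruitment starts and keeps to schedule.

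This is a count of meetings, not of comparative analyses. The earliest meetings would have little outcome data, since T2 follows an 8-week programme and T3 comes 6 months after it.

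**4. What the corresponding author does in recruitment.** Ethical considerations assigns responsibility for coordination. Under Participants, social workers at the centres do the initial screening, and the principal investigators or a research assistant seek consent. The role is therefore oversight of recruitment and consent; whether this person also carries them out is not stated.

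**The case against.** The strongest reply is that the contradiction is one of wording and the harm is not shown. Several parts of that reply stand.

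- **Access by arm is not documented.** A reader might infer that interim results by arm will reach the corresponding author. The article says only that the committee reviews accumulating data and oversees conduct and progress. The data may be pooled, and rules on closed sessions usually sit in a charter or full protocol. The exposure is a possibility that the text does not prevent.
- **Meetings are not looks.** A reader might take the 10 or so meetings as 10 interim comparisons. The article schedules no comparative analysis at any meeting and states no efficacy stopping rule. It mentions interim reports only as an example of when data are locked.
- **Allocation is protected.** Randomization follows consent and baseline assessment, from a computer-generated list handled by a statistician unaware of the study aims. Knowing a trend does not by itself let anyone steer a participant to an arm.
- **Assessment and delivery have safeguards.** The research assistant for outcome assessment and analysis is kept unaware of allocation. Invited instructors deliver the programmes, with independent fidelity checks.
- **Other access may remain.** The Data management section has the investigator verify all collected data. If that is the corresponding author, which is not stated, leaving the committee would not end access to individual records.

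These points narrow the likely routes of bias to conduct decisions and to how the trial is presented and supported. They do not give the committee the independence that the article claims for it.

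**Conclusion.** The point holds in a limited form. The data monitoring committee, as composed, is not independent of trial conduct: one of its four members also sits on the steering committee and is responsible for coordinating the centres, including recruitment and consent. No text in the two sections keeps accumulating results, possibly by arm, from this person at 3-monthly meetings. About 10 of these fall in the recruitment period if the expected dates and the schedule are kept.

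The size of any resulting bias cannot be computed from the documents. The conclusion does not depend on access by arm, on formal interim testing, or on the corresponding author personally enrolling participants, none of which the article establishes. The point does not affect the validity of the primary analysis method. It is a governance defect that should be corrected, since the correction is simple.

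**What to change.** Remove the corresponding author from membership of the data monitoring committee. The independent biostatistician and the two independent experts already named then form it. The corresponding author may attend open sessions only, limited to data pooled over arms.

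If the sponsor prefers to keep the present composition, the protocol should stop describing the committee as independent.

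The cost is a sentence in the protocol and in any charter, with no new members to find. The corresponding author gives up access, through the committee, to any comparative interim data. The investigator's verification of records under Data management is a separate matter that this change does not address.

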### Data processing and analysis

The data will be analysed using SPSS version 26.0 on an intention-to-treat basis. To test the first study hypothesis, we will employ linear mixed models with restricted maximum likelihood estimation to test the individual growth model. This integrated random coefficient approach is usually conceptualized as a two-level model. Level 1, or the within-subject model, is the model used for repeated measures. Level 2, or the between-subjects model, is the model used for time-invariant variables between groups of individuals. The time factor, the grouping factor, and the interaction effect in mixed modelling will be examined. Additionally, the trend depicted in the least square mean plot will be evaluated to determine whether or not any trend-based differences exist between different groups. Hypothesis 1 would be supported if the models assessed and compared are fitted by using appropriate fit statistics. To test hypotheses 2 to 4, macro PROCESS SPSS and the bootstrapping approach will be used to assess the moderated mediation effects in the path model. Each mediator will be mean centred to form the interaction terms. The effects of covariates such as age or gender will be adjusted accordingly. The PROCESS macro is based on ordinary least squares regression. In addition, the mediating effect will be examined by data visualization techniques, such as Trellis coplot, also known as the conditional plot. Hypotheses 2 to 4 would be supported if any mediation effect exists.

The contents of the focus group interviews will be audiotaped and transcribed by a team of independent raters. Thematic analysis will be conducted with the help of the software NVivo (version 12) to store and manage the data. Coding and analysis will involve interpretative phenomenological analysis, which uses a bottom-up approach to determine the themes. Throughout the analysis, the codes will be identified from frequently used words or ideas in the transcripts. The codes will then be categorized into larger recurrent themes for further analysis. The research team will meet to discuss the significance of each theme and to triangulate the results with the quantitative findings.

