The benefits of both MBIs and TCC are reflected in previous research findings. A recently conducted meta-analysis indicates that MBIs show promising effects in regard to the improvement of sleep disturbances [15]. Nevertheless, evidence supports the way in which MBIs are associated with improvements in self-reported outcome measures only [15]. In addition, a recent local study has investigated the effects of mindfulness-based cognitive therapy on insomnia, as compared with sleep psycho-education with an exercise control condition [16]. The investigators found that mindfulness-based cognitive therapy demonstrated short-term benefits for sleep quality only. It is possible that MBIs targeting only cognitive and behavioural vulnerabilities associated with sleep disturbances may therefore produce only limited benefits. Additional focus on physiological and arousal levels may be needed to boost the long-term effects of MBIs. TCC has been shown to emphasize individuals’ control over physical health function and arousal-related responsiveness. Research indicates that TCC provides physiological evidence of its benefits on the autonomic nervous system [17]. A systematic review also found significant benefits of TCC on sleep problems among older adults. However, this evidence is still inconclusive because of the varying quality of these studies and the insufficient fidelity of the intervention implementation to confirm the results [18].

MBIs and TCC represent two distinct forms of mind-body interventions, but they can have a supplementary effect on each other and with a synergetic contribution to ameliorating sleep disturbances. When combining the strength of these two interventions, this integrated intervention may yield a greater treatment effect than using either treatment alone. Therefore, we expect that the integrated mindfulness-based Tai Chi Chuan programme should be more effective and feasible as applied locally.

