### Hypotheses

Hypothesis 1. Participants in the MBTCC group will report significantly greater improvements at 8-week (T2), 6-month (T3), and 12-month (T4) follow-ups in regard to measures of the primary outcome of insomnia severity, compared with participants in the MBI-alone group, the TCC-alone group, and the SHE control group.Hypothesis 2. Participants in the MBI-alone group will experience significantly greater improvements than those in the SHE control group in the primary outcomes across time, in which the beneficial effects on insomnia severity will be mediated by rumination and psychological function.Hypothesis 3. Participants in the TCC-alone group will experience significantly greater improvements than those in the SHE control group in the primary outcomes across time, in which the promising effects on insomnia severity will be mediated by the arousal level and physical function.Hypothesis 4. The favourable effects of the MBTCC group on insomnia severity will be mediated by all the proposed mediators.

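### H1 is about arm differences at T2, T3 and T4, but the stated model tests growth trajectories; if time enters as a straight line, the visit effects can be badly misstated

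*Protocol article*

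**What the plan says.** Under Hypotheses, the protocol article states H1 visit by visit: "Participants in the MBTCC group will report significantly greater improvements at 8-week (T2), 6-month (T3), and 12-month (T4) follow-ups", on insomnia severity, against each of the three other arms.

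Under Data processing and analysis, H1 is tested as follows: "we will employ linear mixed models with restricted maximum likelihood estimation to test the individual growth model". The text adds "This integrated random coefficient approach is usually conceptualized as a two-level model" and "Level 1, or the within-subject model, is the model used for repeated measures". On what is read from the model it says "The time factor, the grouping factor, and the interaction effect in mixed modelling will be examined" and that "the trend depicted in the least square mean plot will be evaluated" for differences in trend between groups. The criterion for H1 is "Hypothesis 1 would be supported if the models assessed and compared are fitted by using appropriate fit statistics".

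The section names no arm contrast at T2, T3 or T4. It does not say whether time is linear, polynomial or categorical, or whether T1 is one of the responses. The only covariates mentioned are age and gender, given as examples after the mediation models. Baseline ISI is collected but not mentioned as a covariate.

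**The concern.** An individual growth model describes each person by a trajectory, and its usual output is a difference in slope. H1 is not a claim about slope. It is a claim about three separate differences, at unequally spaced visits.

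The two agree only if the arm difference grows roughly in proportion to time. Here the group sessions end by T2, and follow-up then runs for a further year. An early drop followed by a plateau or some waning is plausible. The Background itself reports such a pattern for a related therapy: "The investigators found that mindfulness-based cognitive therapy demonstrated short-term benefits for sleep quality only". With that shape, a straight line understates the early effect and implies an arm difference at baseline. It can also turn a real early benefit into a slope that appears to favour the comparator. The coding of time alone could then decide how the primary result reads.

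If time is a categorical factor, a smaller question remains: how T1 is used, and how much precision that costs.

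**Working it through.** **Inputs**
- Visit times (Study design): baseline, end of the 8-week course, and 6 and 12 months after it, taken as t = 0, 2, 8 and 14 months.
- Illustrative effect (pilot Table 1, ISI): difference in change, MBTCC minus SHE = (14.40 - 17.10) - (16.90 - 16.95) = -2.70 + 0.05 = -2.65.
- Evaluable size (Sample size): 180 in total, 45 per arm.
- Correlation rho between visits: not given in the document; .5 and .7 are assumed.

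**Step 1. Straight line, sustained effect.** True differences are 0, -2.65, -2.65, -2.65.
- Mean time is 6; deviations are -6, -4, 2, 8; sum of squares = 36 + 16 + 4 + 64 = 120.
- Slope = (-4 + 2 + 8)(-2.65)/120 = -15.9/120 = -0.1325 per month.
- Mean difference = 3(-2.65)/4 = -1.9875.

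| | T1 | T2 | T3 | T4 |
|---|---|---|---|---|
| True | 0 | -2.65 | -2.65 | -2.65 |
| Fitted line | -1.19 | -1.46 | -2.25 | -3.05 |

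At T2 the fitted difference is 1.46/2.65 = 55% of the truth. Read as change from T1, which is how H1 words it, the line gives only 2(-0.1325) = -0.27 at T2.

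**Step 2. Straight line, waning effect.** True differences are 0, -2.65, -1.325, 0.
- Slope = [(-4)(-2.65) + 2(-1.325) + 8(0)]/120 = 7.95/120 = +0.066 per month. The sign is reversed although MBTCC is better at T2 and T3.
- Complete waning is not needed. If a fraction k of the T2 effect remains at T4, with T3 midway, the slope is proportional to -(9k - 3). It changes sign once k is below 1/3.

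**Step 3. Check with a mixed model.** A 2.5-point effect (the pilot difference in post-treatment means), SD 3.5, rho .5, 45 per arm and visit times converted exactly from weeks give, by generalised least squares, a fitted T2 change effect of -0.23 if the effect is sustained and +0.12 if it fades to 0. Simulated REML random-slope fits gave -0.22 and +0.13 (150 per scenario, many with convergence warnings). For partial fading (-2.5, -1.5, -1.0), the chance of a significant slope difference in favour of MBTCC is about .03, despite a benefit at every follow-up visit.

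**Step 4. Categorical time.** The distortion in Steps 1 to 3 does not arise. With T1 among the responses:
- The group main effect averages four visits, one of them with no expected difference. A sustained effect becomes 3/4 of its size: -1.99 instead of -2.65, a 25% dilution.
- The variance of an unadjusted change-from-T1 contrast is proportional to 2(1 - rho), and that of a baseline-adjusted contrast to 1 - rho². The ratio is 2/(1 + rho): 1.33 at rho .5 and 1.18 at rho .7. Equivalently, adjustment removes 25% or 15% of the variance.
- At 45 per arm, a 0.5 SD effect and rho .5, power for a single two-arm contrast is .66 on change and .78 with adjustment.

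**The case against.** The strongest reply is that the article never says time is linear. A time factor and a plot of least square means both fit categorical time, and comparing models by fit statistics leaves room to compare forms of time. Such details are often left to a fuller document. This stands in part: the figures in Steps 1 to 3 are conditional on a straight line. What the article does state, however, is a growth model with random coefficients and a search for trend differences, and that wording points to continuous time.

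Second, under categorical time the arm-by-time terms do estimate differences in improvement from baseline, which is what H1 asserts. This stands. The dilution affects only the group main effect.

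Third, a reader might infer that the plan gives up baseline adjustment. The document does not support that. It does not state that T1 is a response, it does not rule out a baseline covariate, and a model with T1 as a response and a common T1 mean loses nothing of note.

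Fourth, a reader might infer that all treatment is over by T2. That is also too strong. Daily home practice is advised and monthly reminder calls are planned, so continued gain after T2 is possible. The short-term-only result cited in the Background concerns mindfulness-based cognitive therapy, not MBTCC. Plateau and waning are therefore plausible scenarios, not predictions.

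Fifth, modelling only T2 to T4 with baseline as a covariate drops anyone without a follow-up ISI, which matters with 30% attrition assumed. This stands, and it is why the version with a common T1 mean is put first below.

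**Conclusion.** The point holds in conditional form. The model stated for H1 is aimed at trajectories and trends, while H1 is about arm differences at three visits.

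- **If time is linear** (likely, not stated), the pilot-sized effect held throughout is fitted as -1.46 at T2 and -3.05 at T4, with a false -1.19 at T1. The slope difference reverses (+0.07 per month) if the benefit has gone by T4.
- **If time is categorical**, there is no such distortion. What remains is a 25% dilution of the group main effect for a sustained benefit, and a variance 1.33 or 1.18 times larger than necessary if change from T1 is used unadjusted. This is a loss of precision and not a bias.

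The sizes rest on the pilot difference, rounded visit times, assumed profiles and assumed correlations. The document does not show that the trial will get a wrong answer. It leaves the primary reading open to the form of time, and a better-matched model is available at little cost.

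**What to change.** State the H1 model as a linear mixed model for ISI with visit as a categorical factor, arm, arm-by-visit and an unstructured within-person covariance, in one of two forms:

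1. All four visits as responses, with arm means constrained equal at T1. Baseline is assessed before randomisation, so the constraint is justified by design, and every randomised participant stays in the analysis.
2. Alternatively, T2 to T4 as responses, with baseline ISI and baseline-by-visit as covariates.

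Read H1 from the estimated MBTCC differences against each comparator at T2, T3 and T4. Keep the growth curve and the least square mean plot as descriptive.

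The cost is wording and a different SPSS MIXED specification, with no new data. The unstructured covariance over four visits has 4 × 5/2 = 10 parameters, against 4 for a random intercept and slope with their covariance and one residual variance. The change should be made before outcome data are seen by arm.
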